## Abstract

**Introduction::**

As one of the most prominent public health and medical problems, Chronic Obstructive Pulmonary Disease (COPD) has a serious impact on the quality of life of participants and may even be life-threatening. While modern medicine has worked well to alleviate the symptoms of COPD, the current situation with this chronic disease is not encouraging. Lung-spleen qi deficiency syndrome is one of the common forms of COPD and the traditional Chinese medicine formula Modified Shenling Baizhu Powder is very frequently used in the treatment of this syndrome. However, no direct evidence is available to support the efficacy and safety of Modified Shenling Baizhu Powder for COPD treatment.

**Methods::**

The study is a prospective, randomized, placebo-controlled, double-blind trial in which 270 eligible participants will be randomly assigned to either the experimental or control group in a 1:1 ratio. Both groups will receive the standard Western medication. Meanwhile, participants in the experimental group will undergo Modified Shenling Baizhu Powder, while those in the control group will undergo a matched placebo. The course of treatment is 6 months with 12 months of follow-up. Primary outcome is the forced expiratory volume in 1 second (FEV1) after bronchodi-lator use. The secondary outcomes include the declines and the between-group difference in the change from baseline to 18 months in FEV1 before bronchodilator use; the forced vital capacity (FVC), FEV1/FVC, FEV1%pred after bronchodilator use, modified British medical research council, COPD Assessment Test, St George's Respiratory Questionnaire (SGRQ); frequency, interval, duration and severity of COPD exacerbations; time to first COPD exacerbation; administration of rescue medication and a cost-effectiveness analysis; Smoking status. A safety assessment will also be performed during the trial.

**Discussion::**

The results of this trial will provide comprehensive evidence of the efficacy of Modified Shenling Baizhu Powder for early-stage COPD and the potential mechanism by which Modified Shenling Baizhu Powder acts, which may provide reference for the treatment plan of COPD participants.

**Trial registration::**

ChiCTR2000037873, Registered 2 September 2020

## Introduction

1

Chronic obstructive pulmonary disease (COPD) is the third leading cause of death worldwide.^[1]^ and contributes to high morbidity and mortality in China.^[2]^ Exacerbations of COPD negatively affect ^[3]^ the condition of the participants’ health and result in a rapidly increasing risk of death, which brings them huge economic and psychological burden.

According to The Global Initiative for Chronic Obstructive Lung Disease (GOLD),^[4]^ the prevention of exacerbations is the major treatment goal for participants with COPD. A large epidemiological study released by the Chinese Center for Disease Control and Prevention in 2018 showed that up to 92.7% of Chinese adult COPD patients are in GOLD stage 1–2,^[5]^ presenting with now very mild or no significant respiratory symptoms, such as movement restriction and dyspnea.^[6]^ For them, the prevention of exacerbations is of great significance.

Traditional Chinese medicine (TCM) has gradually gained worldwide recognition. TCM, which many participants suffered from COPD turn to for help in China, may provide further options for COPD treatment.^[7]^ Recorded in formulary of peaceful benevolent dispensary, Shenling Baizhu Powder has been used in China for more than 900 years, and its clinical efficacy and safety are recognized. Modified Shenling Baizhu Powder comprises 12 herbs including LABLAB SEMEN ALBUM (Bai bian dou), ATRACTYLODIS MACROCEPHALAE RHIZOMA (Bai zhu), PORIA(Fuling), PLATYCODONIS RADIX (Jie geng), NELUMBINIS SEMEN (Lian zi), CODONOPSIS PILOSULA (Dang shen), AMOMI FRUCTUS (Sha ren), DIOSCOREAE RHIZOMA (Shan yao), COICIS SEMEN (Yiyiren), GLYCYRRHIZAE RADIX ET RHIZOMA (Gan cao), Ephedrae Herba (Ma huang), ARMENIACAE SEMEN AMARUM (Ku xing ren).

According to Modern pharmacological studies, Modified Shenling Baizhu Powder has multiple effects such as anti-inflammatory, relieving asthma, antibechic, eliminating phlegm, antioxidant,^[8]^ and the function of immune regulation^[9]^ and improving lung function.^[10]^

In China, Shenling Baizhu Powder is widely used for respiratory diseases. Thus, it is reasonable to hypothesize that Modified Shenling Baizhu Powder is effective for the treatment of COPD. However, few published data show a meaningful effect of Modified Shenling Baizhu Powder on preventing exacerbation and its long-term (18 months) safety profile in participants with COPD of GOLD stage 1 or stage 2. To resolve these issues, we design this randomized, placebo-controlled , double-blind, prospective study protocol.

## Methods/design

2

### Design

2.1

This is a randomized, double-blind, prospective, placebo-controlled trial that will enrol 270 participants with COPD of GOLD stage I or stage II. Participants will be screened after obtaining written informed consent and then randomly assigned to the experimental group or control group in the ratio of 1:1. They will be randomly assigned to receive either 10 g of Modified Shenling Baizhu Powder or a placebo 3 times a day for 6 months while receiving standardized Western medical treatment, and will be followed for 12 months. This study will comply with the Standard Protocol Items: Recommendations for Interventional Trials (SPIRIT) 2013 statement^[11]^ (The SPIRIT figure for registration, intervention, and assessment is shown in Fig. 1; the SPIRIT checklist is in Additional file 1) The flow chart of the study is depicted in Figure 2.

**Figure 1 F1:**
[figure not shown]
SPIRIT figure: Schedule of enrollments, interventions, and assessments: [1] Lung function tests: forced expiratory volume in 1 second (FEV1), forced volume capacity (FVC), FEV1/FVC; FEV1%pred; [2] mMRC = modified British medical research council; [3] CAT = COPD Assessment Test; [4] SGRQ = St George's Respiratory Questionnaire; [5] safety assessment = blood routine examination, urine routine examination, stool routine examination, liver function test, kidney function test, electrocardiography.

**Figure 2 F2:**
[figure not shown]
Illustration of the design for clinical studies.

### Ethics approval

2.2

This study was in accordance with the Declaration of Helsinki (Edinburgh 2000) which has been registered with the Chinese Clinical Trials Registry in 2020 (registration number: ChiCTR2000037873). The study protocol was approved by the China Ethics Review Committee for Registered Clinical Trials (Approval No:ChiECRCT20200227), and its design and implementation were followed up by members of the Ethics Committee. The approval of the Ethics Committee must again be sought for any changes to the protocol.

### Recruitment

2.3

Participants will be recruited either through the community or through the outpatient department of the Hospital of Chengdu University of TCM (Chengdu, China), where respiratory physicians will screen participants based on inclusion and exclusion criteria. Prior to registration, participants will be informed of details of the clinical study, including its purpose, handling, schedule, and possible risks and benefits, and an informed written consent form must be signed by all participants to be included in the study.

### Sample size

2.4

The sample size was calculated on the primary outcome (the forced expiratory volume in 1 second (FEV1) at 18 months). According to the previous literature,^[10]^**t**he mean value of FEV1 in the control group is estimated to be 2.54 with a standard deviation of 0.65. After the herbal treatment the mean value of FEV1 in the experimental group is 2.83 with a standard deviation of 0.73. The calculation of the sample size for the experimental and control groups of each was 121 cases using the software Power Analysis and Sample Size version 11.0 (PASS 11.0). Altogether, 268 participants are recruited at a 10% dropout rate. For the actual study, 135 cases per group will be included.

### Randomization and allocation concealment

2.5

We will use the Central Random System to realize random grouping and random hiding. Subsequent to obtaining written informed consent, 270 random order numbers will be generated by members of the Sichuan TCM evidence-based Medicine Center using SAS 9.2 software (SAS, Cary, NC), and eligible participants will be randomly divided into experimental or control groups at a ratio of 1:1. This process is realized by the network version of the central random system, in which the researchers input the screening information of the expected subjects on the central random system, obtain the subject number, meet the subject standard, and sign the informed consent, and then randomly group and generate the random number, The grouping information of the subjects could not be foreseen by the subject and the researcher, and the random number was systematically managed by Sichuan Evidence-based Medicine Center of Traditional Chinese Medicine. Until the end of the study, the subjects, clinicians, and outcome measures were not aware of the grouping of the subjects.

### Blinding

2.6

This trial is a double-blind design in which both participants and researchers will not have any awareness of their treatment group during the trial. Herbal and placebo granules are manufactured, packaged, and labeled by Department of Pharmacy, Hospital of Chengdu University of TCM. to assure consistent appearance, shape, odor and specifications. Furthermore, the research team will be instructed not to interact with participants regarding their potential treatment groupings. Researchers should only report to the principal investigator to decide if exposure blinding is appropriate in emergencies, such as serious adverse events, or when the patient requires urgent treatment

### Diagnostic criteria

2.7

Participants are required to fulfill both the Western medicine diagnostic criteria for COPD (Table 1)^[4]^ and the TCM syndrome diagnostic criteria for lung-spleen qi deficiency syndrome (Table 2).^[12]^ The determination of syndrome differentiation must be made independently by 2 designated TCM associate physicians.

**Table 1 T1:**

Western medicine diagnostic criteria for chronic obstructive pulmonary disease^[4]^.

**Table 2 T2:**
[figure not shown]
Diagnostic criteria for traditional Chinese medicine differentiation of lung-spleen qi deficiency syndrome^[12]^.

### Eligibility criteria

2.8

Inclusion criteria:

1.Age range 40–85 years, male or female2.Grade 1–2 of the COPD diagnostic criteria in GOLD guidelines^[4]^: 20 minutes after inhalation of salbutamol 400, FEV1/FVC <70%, and 50% predicted value ≤FEV1<80% predicted value3.Participants are in the stable stages of COPD and had no respiratory infections or acute exacerbations of COPD within the past 4 weeks4.Participants who meet the diagnostic criteria for common TCM syndromes with lung-spleen qi deficiency syndrome5.Participants volunteer to take part in the study and to provide informed written consent

Exclusion criteria:

1.Patients with chronic lung diseases in which intervention or treatment is required, such as interstitial lung disease, bronchial asthma, active tuberculosis, or bronchiectasis2.Patients with a combination of severe primary diseases, such as cardiovascular and cerebrovascular diseases, liver and kidney diseases, hematopoietic system diseases, endocrine diseases, severe mental disorders, malignant tumors3.Patients have evidence of alcohol or drug abuse, known or suspected allergy to the study drug or some of its components, and currently uses oral corticosteroids regularly4.Women who are breast-feeding, pregnant, or expecting a child5.Patients who have been involved in any other clinical study in the past 6 months6.Patients unable to successfully use a dry powder inhaler or perform pulmonary function measurements

### Termination and withdrawal criteria

2.9

All participants will be notified of their right to stop treatment and withdrawal from the study on any grounds at any time, and the reason for withdrawal will be documented in the case report form (CRF). They will get standardized treatment if they withdraw. The following criteria are used to stop treatment and withdraw from the study project:

1.Patients with severe allergies to the study drug in the course of treatment cannot continue to participate in the clinical study.2.The participant has poor compliance or is taking other medications prohibited by this study protocol.3.Loss of follow-up or voluntary withdrawal from the trial.

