### Treatment plan

3.1

Standards Western medicine will be used for both groups. According to GOLD^[4]^ and the Guidelines for the Diagnosis and Treatment of Chronic Obstructive Pulmonary Disease (Revised 2013),^[13]^ participants will receive inhalation treatment with tiotropium bromide powder (Si Li Hua, Boehringer Ingelheim Pharma GmbH & amp; Co. KG [Germany], 18 μg×30 capsules), 18 μg per inhalation, once a day. Also, the proper use of inhalants will be taught to all participants, who would also have to stop smoking and prevent colds. Throughout the study, patients are not allowed to receive other COPD-related medications or herbal treatments except in emergencies.

Experimental group: Participants will take 10 g Modified Shenling Baizhu Powder 3 times daily, dissolved in 100 mL of warm water, for 6 months.

Control group: participants will receive 10 g placebo granules 3 times daily, dissolved in 100 mL of warm water, for 6 months. The measurements will be in accordance with the experimental group.

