### Outcome measures

3.2

Primary outcome: FEV1 after bronchodilator use at 1, 3, 6, 9, 12, 15, 18 months

Secondary outcomes: at 1, 3, 6, 9, 12, 15, 18 months

1.the declines, the between-group difference in the change from baseline to 18 months in FEV1 before bronchodilator use, FVC, FEV1/FVC, FEV1%pred after bronchodilator use;2.the changes in mMRC score, CAT score, SGRQ score;3.Frequency, interval, duration, and severity of COPD exacerbations; time to first COPD exacerbation; and the use and cost-benefit analysis of rescue medications; smoking status; safety assessment.

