### Statistical analysis

3.7

The intention to treat principle will be followed for all data analysis. The Statistical Package for the Social Sciences version 22.0 (SPSS 22.0, Chicago, IL) will be used to analyze the data. The analysis method should be based on the characteristics of the data distribution: The measurement data will be expressed as mean ± standard deviation and normal distribution, paired *t* test will be used for comparison before and after treatment, *t* test will be used for between-group comparisons (homogeneity test of variance will be performed with 0.05 as the test standard), and rank sum test will be used for comparison between groups. Chi-square test will be used for enumeration data, and rank-sum test will be used for grading data. Bilateral tests will be used for all tests, with *P* < .05 indicating a significant difference. For baseline data, the full analysis set (FAS, including completed cases and dropout cases, excluding censored cases) is used, and the full analysis set and the per-protocol set(PP set, including completed cases, excluding dropout cases and censored cases) are used for efficacy evaluation, which can enhance the reliability of trial results when the conclusions of the two analyses are consistent. When inconsistencies arise, differences should be fully discussed and explained. In the analysis of the full analysis set, the missing data are substituted by the method of sequence mean value.

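### Section 2.9 withdraws participants from the study for poor compliance or non-emergency prohibited medication, so obtainable FEV1 data up to month 18 may go uncollected

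*Protocol article*

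**What the plan says.** Section 2.9 (Termination and withdrawal criteria) opens its list with "The following criteria are used to stop treatment and withdraw from the study project". Item 1 is severe allergy to the study drug, item 2 is "The participant has poor compliance or is taking other medications prohibited by this study protocol", and item 3 is loss to follow-up or voluntary withdrawal.

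Section 3.1 (Treatment plan) says which medication is prohibited and for how long: "Throughout the study, patients are not allowed to receive other COPD-related medications or herbal treatments except in emergencies". It limits the granules or placebo to 6 months. Tiotropium is prescribed for both groups with no stated end. The abstract gives the timetable: "The course of treatment is 6 months with 12 months of follow-up".

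Section 3.2 (Outcome measures) sets "Primary outcome: FEV1 after bronchodilator use at 1, 3, 6, 9, 12, 15, 18 months". The secondary outcomes include exacerbations, "time to first COPD exacerbation; and the use and cost-benefit analysis of rescue medications". Section 2.4 sizes the trial on FEV1 at 18 months.

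Section 3.7 (Statistical analysis) states: "The intention to treat principle will be followed for all data analysis". It describes the full analysis set as "FAS, including completed cases and dropout cases, excluding censored cases" and fills missing values in that set with a sequence mean.

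**The concern.** Stopping a study drug and leaving a study are separate decisions, and section 2.9 merges them. Poor compliance and added medication occur after randomisation and may be related both to arm (tolerability, perceived benefit) and to outcome (a patient who is getting worse is more likely to be given another COPD drug). Neither prevents spirometry.

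If such participants are withdrawn, the trial discards data that the intention-to-treat principle needs and replaces them with a mean, or excludes the participants altogether if they count as censored, a term section 3.7 does not define. The comparison then drifts towards participants who complied and did not need more treatment. An analysis plan cannot recover visits that never took place, so this has to be settled in the conduct rules.

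**Working it through.** **1. Does item 2 mean leaving the study?** The lead-in joins the two actions with *and*. Item 1 says that the patient can no longer take part in the clinical study, and item 3 concerns withdrawal from the trial, so the items on either side of item 2 both mean leaving. Section 3.5, by contrast, stops only the intervention after a serious adverse event. The protocol can therefore separate the two actions, and section 2.9 does not. Section 2.9 makes no provision for visits after withdrawal.

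**2. When does it apply?** The medication ban covers all 18 months and the granules cover the first 6. From month 6 to month 18 there are no granules left to stop, so in those 12 months item 2 mainly affects study participation. Protocol tiotropium may continue, so it is not the only treatment question left.

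**3. What is lost per participant?** FEV1 visits are at months 1, 3, 6, 9, 12, 15 and 18 (7 visits).
- Withdrawn after month 3: misses 6, 9, 12, 15, 18, which is 5 of 7.
- Withdrawn after month 6: misses 9, 12, 15, 18, which is 4 of 7.
- Withdrawn after month 12: misses 15, 18, which is 2 of 7.

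Month 18 is missed in every case.

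**4. Power.** Inputs from section 2.4: means 2.54 and 2.83 (difference 0.29), SDs 0.65 and 0.73, 10% dropout, 135 per group. Two-sided 0.05 is from section 3.7. Power is not stated.
- Pooled SD = √((0.65² + 0.73²)/2) = 0.691.
- Assuming 90% power, n = 2 × (1.960 + 1.282)² × 0.691² / 0.29² gives 120 per group by the normal formula. The noncentral t version gives 121, the plan's figure. At 80% power the normal formula gives 90, so 90% is the value that fits.
- 121/(1 − 0.10) gives 135 per group, as planned.
- Noncentral t power by total share without a month-18 value (anything above 10% is an assumption): 10% (n = 121) 90.2%; 15% (n = 114) 88.4%; 20% (n = 108) 86.6%.

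**5. Bias, illustration only.** Every withdrawal share and deficit here is an assumption. Let w be the share withdrawn under item 2 and D the amount by which their FEV1 lies below that of completers. If those withdrawn are excluded, or filled with their own arm's mean,

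bias = w_E × D_E − w_C × D_C.

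- w = 0.15 and 0.05, common D of 0.1 to 0.5 L: 0.10 × 0.1 = 0.01 L to 0.10 × 0.5 = 0.05 L (3% to 17% of 0.29 L). Reversing the imbalance reverses the sign.
- w = 0.10 in both arms, D_E = 0.5 L, D_C = 0.1 L: 0.05 − 0.01 = 0.04 L (14%).
- w and D the same in both arms: zero.

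The result also depends on which mean is used. In the second case, suppose completers differ by 0.29 L. With everyone followed the difference is 0.29 − 0.04 = 0.25 L. Filling with a mean pooled over arms gives 0.90 × 0.29 = 0.261 L, a bias of about 0.011 L (4%) instead of 0.04 L. Section 3.7 does not say whether the sequence mean is taken by arm or pooled.

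**The case against.** The best defence is that section 2.9 never says that visits or spirometry stop, and that section 3.4 promises reasonable follow-up efforts for everyone after randomisation. A condensed article may also leave the detail to the full protocol. It is true that loss of data is not stated outright. But section 3.4 is general and does not say that people withdrawn under section 2.9 remain in follow-up. At best the two sections pull in different directions, and sites need one rule.

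Four stronger readings are tempting, and the documents do not support them.
- *After month 6 the rule can only mean leaving the study, because no treatment remains.* This holds for the granules only; tiotropium has no 6-month end.
- *Any treated exacerbation leads to withdrawal.* Section 3.1 exempts emergencies. What remains is non-emergency added COPD medication, herbal use and poor compliance.
- *The FEV1 result will be biased by a given amount, or type I error inflated to a given level.* No withdrawal rate or deficit is documented. The 15% against 5% example averages 10%, the whole dropout allowance, and deficits of 0.5 and 0.1 L differ fivefold between the arms of a double-blind trial. If granules and placebo do not differ in any respect, the arms are exchangeable and the expected bias is zero.
- *Only withdrawn consent should end follow-up.* That ignores loss to follow-up and overrides the severe-allergy item without argument.

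The undefined censored cases and the mean substitution are separate weaknesses. They determine where the lost data end up but are not the point here.

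**Conclusion.** The point holds as a badly fixed conduct rule that should be changed. Followed as written, section 2.9 ends study participation for poor compliance or non-emergency prohibited medication. FEV1, exacerbation and rescue-medication data that could be obtained up to month 18 are then not collected, contrary to the intention-to-treat statement in section 3.7.

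This may bias the FEV1 comparison. The number affected is unknown, and the bias can go either way or be zero. The illustrative 0.01 to 0.05 L rests wholly on assumed rates and deficits and on exclusion or an arm mean. Power is secondary: about 3.5 percentage points if total loss doubled from 10% to 20%, taking the back-calculated 90% as the design power. The conclusion rests on reading the joint lead-in literally, which the neighbouring items support.

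**What to change.** Amend section 2.9 to separate stopping the granules from ending follow-up.
- **Poor compliance or prohibited medication:** at most stops the study granules and defines exclusion from the per-protocol set. All scheduled visits, spirometry and recording of exacerbations and rescue medication continue to month 18, and the participant stays in the full analysis set with observed data.
- **Severe allergy:** stop the granules and continue visits where this is safe and the participant agrees.
- **End of follow-up:** only for withdrawn consent or loss to follow-up.

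The cost is a short amendment, which needs ethics approval under section 2.2, and some extra effort to keep participants attending after they stop the granules. The visits are already scheduled, and the sample size does not change.
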